### Socio-demographic and clinical data collection

Once entering the eligible and consenting patient for the first time in the study project, a patient’s ID number will be automatically generated. The Investigator will place this ID number onto the cover page of the PRO Survey Booklet. Only the patient’s ID number will be used when combining PROs data (completed by patients) to clinical data completed by Investigators. In addition to the “Registration Checklist”, this study has three basic case report forms (CRFs) that have been designed to be completed by Investigators at predefined time-points. These CRFs will be provided in the Investigator’s file and set up for the project in the web-based data collection system. Overview of data collection is depicted in Fig. 1.

**Fig. 1 Fig1:**
[figure not shown]
Overview of Data Collection. Abbreviations: *CFRs* Case Report Forms; *PRO* Patient Reported Outcome

#### Baseline history CRF

The Baseline History CRF will include questions related to physician’s backgrounds, including: age, gender, years of experience in treating MM patients and number of patients routinely seen at the center. In addition, clinical information about patient’s diagnosis and treatment will be collected. This form will have to be completed by physicians at the time of patient registration into this study. Data from this CRF will be used in order to compare relevant patient characteristics of those returning PRO information and those who do not during the study period. Most importantly, the frailty score [6] will be evaluated at baseline as this is crucial for the purpose of the study. The CRF will require a number of clinical and laboratory variables, including: date of birth, date of initial diagnosis, gender, living arrangements, education, employment status, ECOG Performance status, laboratory data (serum albumin, creatinine, calcium and lactate dehydrogenase, β2 microglobulin; hemoglobin, platelets counts, leukocyte, granulocyte, and cytogenetic risk at study entry); number and type of previous treatments (including transplantation auto or allo), International Staging System (ISS) at initial diagnosis.

Investigators will also be asked to complete few additional questions to further investigate clinical decision-making process and geriatric assessment. Questions will include: physician’s perception on patient’s role in treatment decisions using an adapted version of the Control Preference Scale [37, 38]. Also, physicians will be asked whether their patients requested prognostic information on survival and to what extent they were involved in making treatment decisions. Frailty score evaluation [6] including the following indices: ADL [7], IADL [8] and Charlson Comorbidity Index (CCI) [9] will also have to be completed.

#### Treatment summary CRF

The Treatment Summary CRF will serve to summarize details of treatment history and will require information on the type, duration and schedule of each treatment received since study inclusion. Patients will be expected undergo various treatments that can generally be classified into the following broad treatment categories (which can be selected either one or more than one): 1) Immunomodulatory drugs (ImiDs) based regimens 2) Protease inhibitors (Pis) based regimens; 3) monoclonal antibodies (MoAbs); 4) chemotherapy; 5) Histone Deacetylases Inhibitors (HDACs). Data to be included in this CRF will be updated throughout the study period.

#### Follow-up CRF

The Follow-up CRF should be completed by physicians at 3, 6, 12, 24 and 30 months. Except for the evaluation at 30 month, these timepoints are in conjunction with PRO assessments. Data to be collected includes: status of patient (dead, alive or lost to follow-up/date of last follow up, date of progression and date of death), disease and treatment related complications, ECOG Performance status, and treatment discontinuation, so as previously defined in the report by Palumbo and colleagues [6]. Adverse events will also be recorded according to the NIH-defined common toxicity criteria CTCAE (Common Terminology Criteria for Adverse Events) version 4.0.

### Patient-reported outcomes (PROs) data collection

Patients will be asked to complete a PRO Survey Booklet that will include previously validated questionnaires and additional ad hoc questions. The ad hoc questions, for example, will investigate on desire for prognostic information on survival and importance of HRQOL aspects in treatment decisions, job problems, and importance placed on “quality of life” considerations when making treatment decisions. PRO assessment is scheduled at the following timepoints: baseline (i.e., at the time of enrolment) and thereafter at 3, 6, 12 and 24 months. PRO baseline assessment has to be performed in the Hospital. A detailed summary of specific PRO questionnaires to be administered at different time-points is reported in Table 1.

**Table 1 Tab1:** Summary of Patient-Reported Outcomes by timing of assessment

PRO Baseline Assessment (at study entry)	
Concept	Data source
Generic Quality of Life	EORTC QLQ-C30
Disease specific Quality of Life	EORTC QLQ-MY20
Information Provision	EORTC QLQ-INFO25
Patient’s perception of involvement in treatment decisions	Adapted Control Preference Scale
Satisfaction with care, prognostic information and personal values	Ad hoc questions
PRO follow-up assessments (3, 6, 12 and 24th month)	
Concept	Data source
Generic Quality of Life	EORTC QLQ-C30
Disease specific Quality of Life	EORTC QLQ-MY20

Following aspects will be investigated:

#### Cancer generic quality of life (EORTC QLQ-C30)

The EORTC QLQ-C30 is a brief multidimensional HRQOL measure consisting of 30 items and includes five functional scales (physical, role, emotional, social, and cognitive), three symptom (fatigue, nausea and vomiting and pain) and a global health status/HRQOL scale and six single items (dyspnea, insomnia, appetite loss, constipation, diarrhea and financial difficulties). The validity and test-retest reliability of this questionnaire is highly consistent across different language-cultural groups [39].

#### Disease specific quality of life (EORTC QLQ-MY20)

The EORTC Quality of Life Questionnaire Multiple Myeloma Module 20 (EORTC QLQ-MY20) will be used to assess disease-specific complaints [40]. This questionnaire contains two symptom scales on disease symptoms and side effects of treatment, one functional scale on future perspective, and one single item on body image.

#### Information provision (EORTC QLQ-INFO25)

The Information provision will be assessed with EORTC QLQ-INFO25 [41]. This 25-item questionnaire includes four information provision subscales: perceived receipt of information about the disease (four items regarding diagnosis, spread of disease, cause(s) of disease and whether the disease is under control), medical tests (three items regarding purpose, procedures and results of tests), treatment (six items regarding medical treatment, benefits, side-effects, effects on disease symptoms, social life and sexual activity) and other care services (four items regarding additional help, rehabilitation options, managing illness at home, psychological support).

#### Patient’s perception of involvement in treatment decisions (control preference scale)

In addition to the above reported PRO measures, an adapted version of the “Control Preference Scale” (CPS) [37, 38] will be used to assess the patient’s perception of who actually made the decision for the current treatment. This adapted version was used in other similar studies [28]. Patients will simply be asked to select one of five statements that best reflects their recall of who actually made the decision for the current treatment (if any at the time of assessment).

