**Methods:**

This multicenter prospective observational study will consecutively enroll 312 patients with multiple myeloma who have received at least 1 prior line of therapy and are considered as RRMM according to the International Myeloma Working Group (IMWG) criteria. Eligible RRMM participants will be adults (≥ 18 years old) patients and will be enrolled irrespective of comorbidities and performance status. At the time of study inclusion, data to calculate the frailty score are to be available. Patients will be followed up for 30 months and patient-reported outcome (PRO) assessment is planned at baseline and thereafter at 3, 6, 12, and 24 months. The following PRO validated questionnaires will be used: the European Organisation for the Research and Treatment of Cancer Quality of Life Questionnaire-Core 30 (EORTC QLQ-C30), the EORTC QLQ-MY20 and the EORTC QLQ-INFO25. Satisfaction with care and preference for involvement in treatment decisions will also be evaluated. Clinical, laboratory and treatment related information will be prospectively collected in conjunction with pre scheduled PRO assessments. Cox regression analyses will be used to assess the prognostic value of baseline fatigue severity (EORTC QLQ-C30) and other patient-reported health-related quality of life parameters.

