Another broad objective of CLARITY is that of generating data that may facilitate physicians to more effectively communicate with their patients and to better respond to individual needs and preferences. In situations for which several different treatment options are available, as it is the case for salvage therapies, and the choice of strategy depends on individual patient characteristics and preferences, shared decision making has been advocated [16, 17]. Shared decision making between patients and physicians may result in a variety of benefits, including increased patient satisfaction and improved clinical outcomes [18–20]. Ideally, patients should be encouraged to participate in decision-making with accurate knowledge about the risks and benefits of all the potential treatment options [21]. However, empirical work suggests that a collaborative treatment strategy might not be ideal for all patients [22, 23], for example, in older patients with more advanced diseases and reduced health conditions [24, 25]. Therefore, physicians should empathetically invite patients to engage to the maximum extent they desire in making treatment decisions [26]. Understanding the extent to which RRMM desire to be involved in making treatment decisions and how this perception is concordant with the understanding of their physicians is important to lay the groundwork for the development of more effective communication strategies. The majority of studies in this area have focused on breast cancer patients [27, 28] and other cancer populations [22] and there is a dearth of information on this topic for patients with MM. The very few studies that have examined this issue in MM patients have been limited by small sample size [29] hampering definitive conclusions.

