### Aims

The primary objective is overall survival (OS) as predicted by baseline self-reported fatigue severity (European Organisation for Research and Treatment of Cancer Quality of Life Questionnaire-Core 30) independently from other known prognostic factors for OS.

The secondary objectives are:to devise a patient-centric frailty score for RRMM patients;to investigate the prognostic value of the frailty score in the setting of RRMM;to investigate HRQOL over time (outcome measures: EORTC QLQ-C30 and QLQ-MY20) by type of treatment and examine factors that contribute the most in maintaining baseline HRQOL levels;to investigate relationship between satisfaction with information provision (outcome measure: EORTC INFO-25) and HRQOL outcomes (outcome measures: EORTC QLQ-C30 and QLQ-MY20);to assess patients’ preferences for involvement in treatment decision-making and the relationships between preferences and patient characteristics.

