#### Secondary outcome analyses

The same analysis as described above will be also performed using the remaining scales of the EORTC QLQ-C30 and those of EORTC QLQ-MY20. We will investigate HRQOL profiles by a repeated measures linear mixed model, reporting estimated means, standard deviations (SDs) and 95% confidence intervals. We will assess the clinical relevance of HRQOL differences among patient groups according to previously published guidelines [47, 48]. The type of missing data generating mechanism will be investigated [49], and sensitivity analysis will be performed to assess the robustness of final results. In addition, the definitive HRQOL deterioration (DD) [50] will be assessed on each EORTC QLQ-C30 scale, based on the corresponding smallest change in the score defining a clinically relevant deterioration [47, 48]. We will also investigate the relationship between satisfaction with information provision and HRQOL outcomes and between preferences and patient characteristics. Statistical significance for all analyses is set as α = 0.05.

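### The aim is preferred involvement in treatment decisions, but the only patient-reported involvement scale described records who actually decided

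*Protocol article*

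**What the plan says.** The Aims section lists, as the last of five secondary objectives, patients' "preferences for involvement in treatment decision-making and the relationships between preferences and patient characteristics". The abstract's Methods paragraph repeats the construct: "Satisfaction with care and preference for involvement in treatment decisions will also be evaluated". The Rationale and clinical significance section gives the motive, which is "Understanding the extent to which RRMM desire to be involved in making treatment decisions", together with how far this agrees with the physicians' understanding. Secondary outcome analyses plans to study the relationship "between preferences and patient characteristics".

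The section on the control preference scale then defines the measure. The adapted scale "will be used to assess the patient’s perception of who actually made the decision for the current treatment", and patients "select one of five statements that best reflects their recall of who actually made the decision for the current treatment". The section adds that this applies only if there is a current treatment when the patient is assessed. Table 1 lists the scale at baseline only, under perception of involvement.

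**The concern.** What a patient would like to happen and what the patient remembers happening are different quantities. The Rationale section relies on that difference. It notes that a collaborative approach may not suit every patient, for example older patients with more advanced disease, and asks physicians to involve patients as far as they themselves wish.

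Take a patient who wanted a shared decision but recalls the physician deciding. The adapted scale records the physician-led role. Suppose such responses were more frequent among older or frailer patients. Reported as preference, the association would say that these patients want less involvement, when the data show only that they recall having had less. The scale's name contains the word preference, although the adaptation described no longer asks about it, so the mislabelling would be easy to make and hard for a reader to notice.

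**Working it through.** No arithmetic applies, and the plan gives no figure for this objective. The check compares the construct named with every measure described that might capture it.

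**Construct named**
- Aims: preferences for involvement, and their relation to patient characteristics.
- Abstract, Methods: preference for involvement.
- Rationale and clinical significance: desired extent of involvement.
- Secondary outcome analyses: relationship of preferences to patient characteristics. The kind of preference is not stated, but the wording matches the aim.

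**Measures described**
- Patient, adapted Control Preference Scale: who actually made the current decision. The section says so twice, once for the purpose of the scale and once for the response task.
- Patient, Table 1: the scale appears under perception of involvement. No row covers preferred involvement, and the follow-up assessments (3, 6, 12 and 24 months) contain only the QLQ-C30 and QLQ-MY20.
- Patient, ad hoc questions (in the PROs data collection section and the section on satisfaction with care): satisfaction with care, with the decision process and with treatment; importance of quality of life when deciding; whether alternatives were discussed; job problems; and desire for prognostic information. The one preference named here concerns disclosure of prognosis, not decision role.
- Physician, Baseline history CRF: the physician's perception of the patient's role on an adapted scale, whether prognostic information was requested, and how far the patient was involved. Whichever role the physician scale refers to, none of these is the patient's own statement of preference.

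**Result**
One objective, and very probably one planned analysis, concern preferred role. No patient item described measures it. The patient measure that is described captures actual role, at baseline only, and only where there is a current treatment.

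**Is this only the brevity of an article?** No. An article may leave the wording of an instrument to the full protocol. Here the article states what the instrument asks, and it differs from what the objective needs.

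**The case against.** The strongest counter-argument is that the PRO Survey Booklet is not shown and the ad hoc questions are introduced only as examples. Table 1 also has an ad hoc category that extends to personal values. A preferred-role question could exist without being listed. This stands, and it limits the claim to the instruments described. A reader might infer that the objective is unanswerable outright, or that none of the 312 planned patients would provide a preference measurement. The documents do not establish either.

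The word preferences in Secondary outcome analyses could also refer to disclosure of prognosis, which is measured and whose associated factors the background section wants to identify. That reading is possible. The sentence more probably echoes the aim, but it is weaker evidence than the Aims section and the abstract.

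A reader might further infer that planned concordance analyses are lost. Agreement between preferred and actual role is not an objective anywhere. Agreement between patient and physician appears in the Rationale section but not among the listed aims, and agreement on perceived role might still be examined, since both complete an adapted scale. So no stated concordance objective fails.

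Finally, the plan specifies no regression for this aim, and the section heading and Table 1 label the construct correctly as perception. Both lower the risk of misreporting. They do not supply the missing measurement, and the aim and abstract still promise preference.

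**Conclusion.** The mismatch is real. With the instruments described, the objective on preferred involvement cannot be answered, and an analysis of the adapted scale would answer a different question: which patient characteristics go with perceived actual involvement in the current treatment decision.

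The scope is one secondary objective and the analysis that serves it. The primary objective, the sample size and the other secondary objectives are unaffected. Patients without a current treatment at baseline would give no response even on actual role; the documents do not say how many these are, so no size can be put on that loss.

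The conclusion assumes that the article describes every patient item relevant to decision role. If the booklet holds an unlisted preferred-role item, the remaining fault is that the article assigns involvement to the wrong measure and does not name the right one. It should be fixed, but it does not threaten the study as a whole.

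**What to change.** If the booklet already contains a preferred-role item, name it in the instrument section and Table 1 and tie the objective to it. If not, add one item to the baseline booklet: the same five statements, worded as how the patient would prefer treatment decisions to be made. Use it for the preference objective, and report the existing scale separately as perceived actual role.

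The cost is one question per patient and a booklet amendment. Recruitment began in November 2017 and was expected to end around November 2018, so a new item would be missing for everyone enrolled before the change. As the section on missing PRO data notes, self-reports cannot be recovered later from charts. An answer given after treatment has been chosen may also be coloured by that decision. Both limits should be stated with the results.

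If the booklet cannot change, reword the aim, the abstract and the analysis sentence to perceived actual involvement in the current treatment decision, and make no claims about preference. That costs only wording, but it gives up the preference question.

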#### Satisfaction with care, prognostic information and personal values (ad hoc questions)

Patients will be asked to rate their satisfaction with care and with the overall decision-making process regarding their care in general (rather than any specific clinical decision). Also, they will be asked to what extent they feel is important (in general) to consider impact of therapy on quality of life when making treatment decisions and whether they discussed with their physician possible alternative treatment options before starting the current therapy. This will make the evaluation in this RRMM setting more feasible considering the variability of potential treatments that patients will receive at the time of study entry. Similarly to previous studies [42] patients will be asked whether they are satisfied with the way treatment decisions were made and whether they are satisfied with current treatment. Also, preference for disclosure of prognostic information will be assessed by formulating questions based on previous research investigating this issue in similar settings [24].

### PROs data collection and management of PROs missing data

Excellent level of compliance on questionnaires is of great importance for the success of the study and efforts should be made to further motivate patients. However, a certain percentage of missing data is quite common and is to be expected. The missing data might present an unusual challenge in that the information provided by a patient’s self-report, as at a particular point in time, the information cannot be retrieved at a later date from medical charts (as it is often possible with other types of clinical non-patient reported data). It is thus important to document and report the extent of and reasons for missing data. Each participating center will be requested to submit a PRO Missing Data Form in lieu of a questionnaire for any assessment that is not provided at the appropriate follow-up time points. The PRO Missing Data Form will be completed by the PRO Liaison Person or the local study coordinator and will request information about the reason(s) for the missed assessment. The appropriate Form will be provided in the Investigator’s file and documented in the data management system.

### Statistical considerations

#### Sample size determination

Based on previous evidence in MM patients [13, 14], the EORTC QLQ-C30 fatigue scale was used to calculate sample size and considered as the primary outcome in this study. We performed a calculation in order to detect, at least, a hazard ratio (HR) of 1.11 for overall survival, for each 10-points increase (i.e. worse score) on the baseline fatigue scale, assuming a baseline standard deviation of 29 points [43]. Based on previous studies and on clinical grounds [44], we also assumed a minimum event rate of 35% during the study and considered a follow-up of 30 months from date of enrolment. Allowing for an alpha error of 0.05 and a power of 90%, the calculated sample size for this group is 296 patients. However, estimating an overall 5% of patients not evaluable for whatever reason, the actual sample size required is 312 patients.

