## Methods/design

### Study design and logistics

This is a multi-center international (Italy and UK) prospective observational study lead by the GIMEMA (Gruppo Italiano Malattie EMatologiche dell’Adulto). All patients enrolled in this study will be followed-up for 30 months from date of registration regardless of their compliance with PRO assessments at pre-scheduled time points. All data will be centrally collected and analyzed at the GIMEMA Data Center, in Rome (Italy). The GIMEMA Data Center will set up all the relevant administrative materials to be sent out to all participating Centers. Data in this study will be collected through a state of the art web-based data management system: REDCap [36].

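### The 296 evaluable patients do not follow from the stated hazard ratio of 1.11; at the minimum 35% event rate, two-sided unadjusted power is about 87%, not 90%

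*Protocol article*

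**What the plan says.** The calculation is in the protocol article under Sample size determination. The effect to be detected, on the baseline EORTC QLQ-C30 fatigue scale, is set as follows: "We performed a calculation in order to detect, at least, a hazard ratio (HR) of 1.11 for overall survival, for each 10-points increase", "assuming a baseline standard deviation of 29 points". On deaths it says "we also assumed a minimum event rate of 35% during the study", and it "considered a follow-up of 30 months from date of enrolment". The result is: "Allowing for an alpha error of 0.05 and a power of 90%, the calculated sample size for this group is 296 patients". A 5% allowance for patients who cannot be evaluated then raises this to 312.

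The section does not say whether alpha is one-sided or two-sided, and it mentions no allowance for correlation between fatigue and other covariates. Primary outcome analysis plans a Cox model that also contains the frailty risk groups and established prognostic factors, with a likelihood ratio test for what fatigue adds to the frailty score. Secondary outcome analyses sets α = 0.05 for all analyses, with no mention of a one-sided test.

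**The concern.** Once the event rate is fixed, the printed inputs determine the unadjusted sample size apart from sidedness, so the figure can be checked directly. The check fails under either sidedness. This is not detail that a condensed article leaves to a fuller document: the inputs and the result are both printed, and they disagree.

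At stake is the only power statement for the primary objective. A sponsor who believes the study has 90% power at the minimum event rate thinks it has more margin than it does. The margin matters because the primary model is multivariable and any correlation between fatigue and the other covariates lowers power further.

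**Working it through.** **Inputs, all from Sample size determination**
- Hazard ratio 1.11 per 10 points, so b = ln(1.11) = 0.10436
- SD 29 points = 2.9 units of 10 points, so SD² = 8.41
- Event rate 35% (called a minimum)
- Alpha 0.05, power 90%, so z = 1.960 (two-sided) or 1.645 (one-sided), and 1.2816
- Not evaluable: 5%

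The 30 months of follow-up do not enter separately once the event rate is fixed.

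**Formulas** (continuous covariate in a Cox model, Schoenfeld / Hsieh-Lavori form; R² is the squared multiple correlation of fatigue with the other covariates)
- Deaths: D = (z_alpha + z_power)² / [SD² × b² × (1 − R²)]
- Patients: N = D / event rate
- Power = Φ(√[D × (1 − R²)] × SD × b − z_alpha)

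**1. Printed inputs, R² = 0**
- Two-sided: D = 10.507 / (8.41 × 0.010891) = 114.7. N = 114.7 / 0.35 = 327.8, so 328. Then 328 / 0.95 gives 346.
- One-sided: D = 93.5 and N = 267.1, so 268.

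The article's 296 is not reproduced. The two-sided figure is 10.8% higher (328 / 296 = 1.108).

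**2. What does reproduce 296**
- With b = 0.11, two-sided: D = 10.507 / (8.41 × 0.0121) = 103.26. N = 295.02, so 296. Then 296 / 0.95 = 311.6, so 312. Both published figures match, and the 5% step is correct.
- exp(0.11) = 1.116, which would print as 1.12 to two decimals, not 1.11.
- Rounding of the hazard ratio alone does not close the gap: 1.1149, which still prints as 1.11, gives 302.
- Two other combinations also reach 296: a hazard ratio of 1.1145 with SD 29.4, two-sided (295.5); or 1.11 with one-sided alpha and R² of about 0.097 (267.1 / 0.903 = 295.8). Neither is stated.

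**3. Power at 296 evaluable for a hazard ratio of 1.11**
- Deaths at 35%: 296 × 0.35 = 103.6
- Two-sided: Φ(√103.6 × 2.9 × 0.10436 − 1.960) = Φ(1.120) = 86.9%, a type II error of 13.1%
- One-sided: 92.4%
- If all 312 are evaluable (109.2 deaths), two-sided: 88.5%
- Event rate that restores 90% two-sided at 296: 114.7 / 296 = 38.8%
- Hazard ratio detectable with 90% power at 103.6 deaths: exp[3.2415 / (2.9 × √103.6)] = 1.116

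**4. Covariate adjustment** (R² values assumed for illustration; the article gives none)

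| R² | Two-sided power at 296, HR 1.11 | N for 90% |
|---|---|---|
| 0 | 86.9% | 328 |
| 0.10 | 83.2% | 365 |
| 0.20 | 78.7% | 410 |

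**The case against.** Four points can be made for the plan.

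First, the cause is not documented. A reader might infer as fact that 0.11 was mistakenly entered as the log hazard ratio. The article does not say so, and the combinations in step 2 show that other unstated inputs also give 296. This stands: the 0.11 explanation is the simplest, and it matches both published figures, but it remains an inference. The mismatch itself does not depend on it.

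Second, sidedness is not stated, and a one-sided test would have 92.4% power at 296. This stands as a condition on the 87%. Two-sided is the more natural reading, because the planned likelihood ratio test is not directional and the general α of 0.05 carries no one-sided qualifier. A one-sided reading would not rescue the calculation either, since it gives 268.

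Third, 35% is described as a minimum. A reader might take 104 as the number of deaths the study expects, and conclude that it will be underpowered. The article does not support that: 104 is the count at its assumed floor. At 38.8% events unadjusted power reaches 90%, and at 40% it is 90.9%. The reply is only that the article's sample size is calculated at 35%, and at that rate the claim of 90% power does not hold.

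Fourth, the loss is small: 3.1 percentage points of unadjusted power, or a detectable hazard ratio of 1.116 in place of 1.11. In an observational prognostic study this changes no treatment allocation, estimand or analysis. That stands too, and it limits the remedy to a restatement.

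**Conclusion.** The stated 296 is wrong for the printed inputs: without adjustment they give 328 two-sided or 268 one-sided. At 296 evaluable patients and the minimum 35% event rate, power for a hazard ratio of 1.11 is 86.9% against the 90% claimed, on a two-sided 0.05 test with no covariate adjustment. Read the other way, the sample has 90% power for a hazard ratio of 1.116.

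The non-reproduction is firm under either sidedness. The 87% rests on the two-sided reading and on the event rate being at its stated floor; a higher death rate raises it, and correlation between fatigue and the adjusting covariates lowers it. A reader might infer that the study must enrol 346 patients or follow them for longer. The documents do not support that: the shortfall at the floor is modest, and what is wrong is the stated power or effect size, not the feasibility of the primary analysis.

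**What to change.** Restate the calculation in Sample size determination for the sample already planned. For 312 enrolled (296 evaluable) and the minimum event rate of 35% (about 104 deaths), at two-sided alpha 0.05, give either about 87% power for a hazard ratio of 1.11 per 10 points, or 90% power for 1.116. Print the latter to three decimals, because 1.12 would imply 278 patients. State the log hazard ratio that was used, and add that the calculation is unadjusted for the frailty score and the other covariates in the primary model. It would also help the reader to say that about 38.8% events among 296 patients would bring unadjusted power for 1.11 back to 90%.

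The cost is one or two sentences and a slightly less favourable figure. No change to enrolment, the 30-month follow-up or the analysis is required.
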